### Inclusion criteria (chronic obstructive pulmonary disease)

The inclusion criteria for participation in the trial are as follows:age ≥ 40 years,cumulative (current or previous) smoking history > 10 pack-years, andpostbronchodilator FEV_1_ ≥ 50% predicted Global Initiative for Chronic Obstructive Lung Disease Spirometric stage 3 or 4 [4].

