**Methods/Design:**

This trial is a prospective, assessor-blind, randomized controlled trial. The participants are patients with stable severe to very severe COPD who are older than 40 years of age and healthy controls. The intervention is single-limb, high-repetitive, resistance training with elastic bands, three times/week for 8 weeks.

The control is two-limb high-repetitive resistance training with elastic bands, three times/week for 8 weeks.

The primary outcomes is change in the 6-min walking distance after 8 weeks of single-limb or two-limb high-repetitive resistance training.

The secondary outcomes are changes in limb muscle strength and endurance capacity, key protein involved in quadriceps anabolic/catabolic signalization, fiber-type distribution and capillarization, subjective dyspnea and muscle fatigue, muscle oxygenation, cardiorespiratory demand and health-related quality-of-life after 8 weeks of single-limb or two-limb high-repetitive resistance training.

The acute effects of single-limb versus two-limb high-repetitive resistance training on contractile fatigue, exercise stimulus (the product of number of repetition and load), subjective dyspnea and muscle fatigue, muscle oxygenation, and cardiorespiratory demand during upper and lower limb exercises will also be investigated in patients with COPD and healthy controls.

Randomization will be performed using a random number generator by a person independent of the recruitment process, using 1:1 allocation to the intervention and the control group using random block sizes.

Blinding: All outcome assessors will be blinded to group assignment.

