Lastly, the majority of patients included in this previous research had moderate airflow limitation, whereas high-repetitive single-limb resistance training would appear particularly suited for patients with advanced ventilator limitation. Thus, the overall aim of the current project is to investigate the muscular and functional effects of high-repetitive resistance training, in patients with severe to very severe COPD and to better understand the mechanisms of action of this training modality.

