## Methods/Design

The study is a prospective, assessor-blind, block randomized, controlled, parallel-group trial constructed in accordance to the consolidate standards of reporting trials guidelines [19,20] (Figure 1). The study contains a chronic and an acute phase. In the chronic phase, the benefits of 8 weeks of single-limb and two-limb high-repetitive resistance training will be compared in patients with severe and very severe COPD. The acute phase will be used to investigate, at baseline, the acute physiological effects of single-limb and two-limb high-repetitive resistance training in patients with COPD and also in healthy controls. An overview of the two phases including a description of the testing procedure can be seen in Table 1.

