### Hypotheses

The following hypotheses are proposed:Single-limb high-repetitive resistance training will provide a larger gain in the 6-min walking distance than the two-limb high-repetitive resistance training in patients with severe to very severe (stage 3 to 4) COPD.Eight weeks of single limb high-repetitive resistance training will be associated with larger physiological (muscle endurance, fatigue and deoxygenation) and structural (muscle protein synthesis, fiber-type distribution and capillarization) adaptations to training, and lower cardiorespiratory demand, as well a greater increase in health-related quality-of-life in comparison to two-limb high-repetitive resistance training.Two-limb high-repetitive resistance training will lead to larger restraints on the ventilatory system and higher dyspnea scores and, to reduced muscle fatigue, deoxygenation and localized exercise stimulus in comparison to single-limb high-repetitive resistance training in patients with COPD. Healthy controls will be able to train both legs/arms simultaneously without central constraints and with no differences in muscle fatigue or exercise stimulus between the two high-repetitive regimens.

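### The FEV1 inclusion threshold has its inequality reversed: a floor of 50% predicted contradicts the stage 3 or 4 requirement in the same line and the severe to very severe population stated elsewhere

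*Protocol article*

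**What the plan says.** The section on inclusion criteria for COPD lists three items: age, smoking history and lung function. The third asks for postbronchodilator "FEV_1_ ≥ 50% predicted Global Initiative for Chronic Obstructive Lung Disease Spirometric stage 3 or 4". That one item holds two conditions, a number and a spirometric stage. The limits of the stages are not printed; the item refers to a cited source for them.

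The population is described in four other places, always the same way:

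- Abstract, Methods/Design: "The participants are patients with stable severe to very severe COPD who are older than 40 years of age and healthy controls".
- Background, closing paragraph: the overall aim is set in severe to very severe COPD. The reason given is that "the majority of patients included in this previous research had moderate airflow limitation", whereas single-limb training "would appear particularly suited for patients with advanced ventilator limitation".
- Methods/Design, opening paragraph: the two 8-week programmes "will be compared in patients with severe and very severe COPD".
- Hypotheses: the primary hypothesis is stated "in patients with severe to very severe (stage 3 to 4) COPD". This also fixes the article's own mapping of stage to severity.

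No other section gives an FEV1 threshold, so nothing in the article corrects the number.

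**The concern.** FEV1 as a percentage of predicted falls as airflow limitation worsens. A lower limit of 50%, with no upper limit, points towards mild disease, while the stage label next to it points towards severe disease. The two halves of one eligibility item pull in opposite directions.

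This item is the only one that sets disease severity at entry. Severity is central to the rationale: the primary hypothesis is confined to stages 3 and 4, and the third hypothesis rests on ventilatory restraint during two-limb exercise, which the Background links to advanced disease. Anyone who screens, monitors, replicates or abstracts the trial by the printed number would select the opposite end of the disease range. With 30 patients planned, a few entrants of the wrong severity would be a visible share of the sample.

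**Working it through.** The point is one of logic. The plan has no figure of its own to reproduce here.

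**Inputs**

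- Numeric condition: FEV1 ≥ 50% predicted, no ceiling (COPD inclusion criteria).
- Stage condition: spirometric stage 3 or 4 (same item).
- Stage 3 to 4 means severe to very severe (Hypotheses).
- Stage limits: not printed. Assumption, the usual spirometric grading: stage 3 is 30% to below 50% predicted, stage 4 is below 30%.

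**Step 1: direction, without the assumption.** Let *c* be the upper FEV1 limit of stage 3. The stage condition is FEV1 < *c*, a ceiling. The numeric condition is a floor. Together they admit 50 ≤ FEV1 < *c*. If *c* is 50 or less, this set is empty. If *c* were above 50, it would hold only the mildest edge of the target group. For no value of *c* does the floor select towards the most severe patients.

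**Step 2: the usual staging, *c* = 50.**

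| FEV1, % predicted | Stage (assumed) | Target? | Meets ≥ 50%? | Meets stage 3 or 4? | Meets both? |
|---|---|---|---|---|---|
| below 30 | 4 | yes | no | yes | no |
| 30 to below 50 | 3 | yes | no | yes | no |
| 50 and above | milder than 3 | no | yes | no | no |

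The two conditions disagree in every row.

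**Step 3: grid check.** FEV1 from 10.0% to 100.0% in steps of 0.1 gives (100.0 − 10.0)/0.1 + 1 = 901 values.

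- As printed (≥ 50% and stage 3 or 4): 0 of 901 qualify.
- Number alone (≥ 50%): 901 − 400 = 501 values qualify, none of them stage 3 or 4.
- Inequality reversed (< 50% and stage 3 or 4): all 400 values below 50% qualify.
- With ≤ 50% in place of < 50%, the joint count is again 400, because the stage condition decides at exactly 50.0%.

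These counts describe the rule. They are not estimates of patient numbers.

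**Step 4: does anything else depend on it?** The sample-size statement uses a 34 m difference, an SD of 30 m, two-sided α of 0.05 and 80% power. In the normal approximation, n per group = 2 × (1.960 + 0.842)² × (30/34)² = 2 × 7.85 × 0.779 ≈ 12.2, rounded up to the stated 13. FEV1 does not enter this calculation, and the models named under Statistics do not use it as specified.

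**The case against.** The best defence is that this is an obvious slip. The intended population is given consistently in the abstract, Background, design section and hypotheses, and the disputed item itself names the right stages. Staff who screened by stage would have enrolled correctly. That stands, and it limits the weight of the point, but it does not make the criterion usable as written.

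The symbol might also have been altered when the text was converted. This cannot be fully excluded, since no less-than-or-equal sign appears elsewhere in the text. It is unlikely, because neighbouring criteria print sensible signs (age ≥ 40 years, SpO2 < 85%).

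A further objection is that the replacement threshold rests on staging limits the article does not print. This also stands. What the document alone establishes is that number and stage conflict and must be made to agree; the value of 50% as a ceiling follows from the assumed staging.

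Three stronger readings are tempting, and the document does not support them:

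- A reader might infer that mild or moderate patients were enrolled. Nothing in the article shows this.
- A reader might infer that nobody can tell to whom the results apply. The other sections make the target plain.
- A reader might infer that enrolling moderate patients would repeat a question already answered by the group's earlier trial. The Background says that trial had no active comparator, so single- versus two-limb training was untested in moderate disease too.

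**Conclusion.** The point holds as an internal contradiction in an operative eligibility rule. The numeric half of the FEV1 criterion is reversed relative to the stage requirement in the same item and to every other description of the population. On the assumed staging, the item as printed admits no one, and its number alone admits only patients milder than the target. The direction of the error does not depend on that assumption; the empty intersection and the exact cut-off do.

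The likeliest cause is a one-character error. Sample size and the stated analysis are unaffected. The correction is still needed, because this item decides who enters the trial.

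**What to change.** Reverse the inequality so that the number agrees with the stage: postbronchodilator FEV1 < 50% predicted, spirometric stage 3 or 4, with the cited staging governing a value of exactly 50%. Check the source staging document when making the change, since its limits are assumed here.

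The first patient was randomised on 10 November 2014 and the trial was still recruiting when the article was submitted on 6 January 2015. The sponsor should therefore compare the screening spirometry of everyone randomised with the corrected rule. Any patient outside stage 3 or 4 should be reported as an eligibility deviation and kept in the intention-to-treat set, in line with the commitment under Statistics to analyse all randomised patients in their original group.

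The cost is a one-character correction notice and a review of records already on file. No new patients, visits or procedures are needed.

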### Exclusion criteria

The exclusion criteria for participation in the trial are as follows:recent COPD exacerbation (< 6 weeks),neuromuscular and/or orthopedic disorders that compromise participation to an exercise program,recent cancer,unstable cardiac disease and cardiac stimulator,asthma (current),low body weight or obesity (body mass index < 20 kg/m^2^ or > 30 kg/m^2^),significant hypoxemia at rest (SpO_2_ < 85%), ora daily dose > 10 mg of systemic prednisone.

### Inclusion criteria (healthy controls)

The inclusion criteria for healthy controls are as follows:age ≥ 40 years andnormal pulmonary function.

### Exclusion criteria (healthy controls)

The exclusion criteria for participation as a healthy control are as follows:neuromuscular and/or orthopedic disorders compromising participation to an exercise program orphysically active (> 9) on the Voorips questionnaire [23].

### Description of intervention and control groups

Patients with COPD will be randomized to either single or two-limb high-repetitive resistance training. Identical high-repetitive resistance exercise regimen will be used for both interventions, with one exception; the intervention group will perform the exercise regimen using a single limb at a time while the control group will, depending on exercise, perform the training using either both arms or both legs. A total of three sets will be performed for each limb. Training time will be shorter for the two-limb high-repetitive training group in comparison to the single-limb training group. To minimize any confounding effects of different amount of time spent with research staff, the control group will perform a light intensity balance exercise that will compensate for the difference in training time between the two interventions.

Both interventions will be provided on the basis of three sessions per week for 8 weeks. They will be performed under direct supervision, individually or in small groups of 2 to 4 participants. The care provider supervising the training will receive standardized education before the start of intervention consisting of written, oral and visual instructions on how to perform and instruct the exercises used in both high-repetitive protocols.

Before the actual training, there will be a 5-minute warm-up period on a stationary cross-trainer, focusing on muscle groups that will be trained during various exercises, including the latissimus row (m. latissimus dorsi), chest press (m. pectoralis major and m. deltoid anterior), knee extension (m. quadriceps), shoulder flexion (m. deltoid anterior), leg curl (m. hamstrings), elbow flexion (m. biceps brachii) and plantar flexion (mm. triceps surae). All exercises will be performed with elastic bands (Thera-Bands, The Hygenic Corporation [name]) with the exception of plantar flexion that will be executed using a weight-machine (Sport Art Fitness, Woodinville, WA, USA). Extended description of the exercise programs for the single-limb and the two-limb group including detailed including illustrations of start and end positions as well as execution of exercise movement is explained more in detail in the additional files [see Additional file 1 and 2].

Unilateral or bilateral exercises with high repetitions and low amount of rest (one minute) are selected for this trial in line with recommendations from the ACSM [10]. Moderate to fast velocities is recommended when performing a larger number of repetitions, that is, at least 15 repetitions. Participants will be positioned so that the elastic band(s) are stretched 100% at end of movement for each exercise, respectively. Since the most clinically effective portion of elastic resistance is 25% to 250% elongation, all exercise start and stop positions are within this interval [24]. The relaxed length of the elastic resistance bands from insertion are standardized to 85 cm for each side, pre-stretched 20 times to stabilize the material [25].

Individual starting resistance will be set at 25 repetition maximum (25 RM) in the different exercises. The resistance for each exercise and the progression of resistance will be individually determined. Progression will be done separately for the different exercises in accordance to ACSM recommendations [10]. That is, a participant performing >30 repetitions will result in an increase in resistance. The criteria for progression should be fulfilled in two subsequent sessions or two out of three successive sessions. Resistance will be increased with approximately 10% by changing the tension of the resistance bands or adding weights to the weight machine [10].

Cool down/stretching will consist of four stretching exercises for involved muscle groups. Holding each stretch 30 seconds to mild discomfort, two sets for each limb (that is, two minutes of active stretching for each muscle), in accordance to American College of Sports Medicine recommendations [26].

### Procedure

Participants will perform three visits for the acute phase of the protocol. These visits are also used as baseline testing for patients with COPD who will contribute to the chronic phase of the protocol. The same evaluation will also be performed after the 8-week training program in patients with COPD. Pre- and post-tests will be performed at similar time of day, with the same rest between test occasions and between tests.

Since a subject’s motivation may determine attainment of maximal effort [5], both pre- and post-tests are performed using standardized information and encouragement [27]. No additional follow-up other than directly after end of intervention period is used within this trial. The perception of dyspnea and muscle fatigue will be measured with the modified Borg scale [28] before and directly after all physical tests as commonly and reliably used in patients with COPD [29,14,30].

#### Screening tests

During the first visit, all procedures will be explained and the informed consent form will be reviewed and signed. Participants will then fill the Voorips physical activity level questionnaire that is validated for elderly individuals [23] and applied to patients with COPD [31]. Participants will complete pulmonary function assessment (plethysmography, spirometry) while being on their usual bronchodilator therapy. Anthropometric measurements will include height, weight, body composition and thigh subcutaneous skinfold. The latter is relevant for measurement of muscle oxygenation. Body composition will be assessed by bioelectrical impedance (InBody520, Body Composition Analyzer, Biospace, Seoul, Korea).

### Outcome measures

#### Functional tests

The 6MWT will be used to assess the primary outcome, walking distance [32]. The walking course will be 30 meters in length, and the patients will be instructed in accordance to standardized guidelines [33] to walk as far as possible in 6 minutes. One practice test will be performed to minimize the risk of learning effect. The highest walking distance of the two 6-min walks will be chosen as baseline value.

To measure unsupported upper limb endurance capacity the unsupported upper limb exercise test (UULEX) will be used [34]. Participants will hold a plastic bar (0.2 kg), at shoulder width and will be asked to raise it from hip to the UULEX eight level chart for one minute at each level with a cadence of 30 movements per minute. If a patient reaches the highest level, the plastic bar will be replaced by a heavier one every minute. There are five different bar weights (0.2, 0.5, 1, 1.5, 2 Kg), and participants will continue on the highest level until symptom limitation.

#### Limb muscle function

Limb muscle function will be evaluated in two ways. Muscle strength and endurance will be evaluated during isokinetic knee extension and shoulder flexion using the Biodex Multi-Joint System 4 (Biodex Corp., Shirley, New York). Both knee extension and shoulder flexion will be performed unilaterally on the self-reported dominant side in accordance to manufacturer recommendations. In addition, knee extension will also be performed with both lower limbs in order to compare single to two-limb execution. Each movement will be performed 25 consecutive times using maximal effort during the concentric phase and relaxation during the eccentric phase. Two different aspects of muscle function will be measured. Peak torque from the highest contraction will be used for maximal strength and total work generated from all contractions will be used for endurance. The tests will be performed at an angular velocity of 60° · s^−1^, which is considered ideal for evaluating muscle strength in patients with COPD [35] and is found reliable in endurance testing procedures [36]. Before each test, participants will perform five submaximal contractions to familiarize themselves with the equipment and testing procedures, followed by 2 minutes of standardized rest [27]. Shoulder flexion will be performed between 0° to 90° with the elbow extended and the forearm pronated. Knee extension will be performed between 90° flexion to maximal individual extension minus 5° to lower the risk for a passive resistance from the hamstrings muscles. No visual feedback is given during tests. Standardized encouragement will be given.

Limb muscle function will also be evaluated, during visit two and three of the acute phase and during post assessment in the chronic phase, in the following six resistance exercises: latissimus row, chest press, knee extension, shoulder flexion, leg curl and elbow flexion [37-40]. All exercises will be executed using elastic resistance bands (Thera-Bands, The Hygenic Corporation, Akron, OH, USA) and will be performed seated using the chair of the Biodex Multi-Joint System 4 (Biodex Corp., Shirley, New York, USA). The positioning of the participants will be adjusted so that the elastic resistance band(s) is stretched 100% at end of movement. During one visit all exercises will be performed once using one limb at a time, while during the other visit, exercises will be performed using two limbs simultaneously. The six exercises will be performed for a total of three sets with 2 minutes of rest between exercises and one minute of rest between sets. Participants will be instructed to contract their limb with maximal effort at each repetition, executing the maximal number of repetitions that can be performed. Speed of movement will be standardized to one second in the concentric phase and one second in the eccentric phase with the use of a Metronome. The loading in these exercises is determined from 25 RM tests performed during the first visit of the acute phase, executed in accordance to recommended guidelines [41]. The loadings obtained from the 25 RM tests will also be considered start loading for the high-repetitive resistance training regimens in the chronic phase of this protocol.

In the acute phase and during post assessment in the chronic phase the following physiological variables will be measured while executing the latissimus row, chest press, knee extension, shoulder flexion, leg curl and elbow flexion exercises:*Muscle oxygenation*Muscle oxygenation will be acquired continuously using a surface electrode from a near-infrared spectroscopy system (NIRS) (OxiplexTS, ISS, Champaign, USA) placed on the skin muscle belly.*Cardiorespiratory response*Ventilatory and heart rate responses will be determined using a portable gas analysis system (Oxycon Mobile, Viasys Healthcare, Jaeger, Germany). Minute ventilation (VE) oxygen uptake (VO_2_), carbon dioxide excretion (VCO_2,_), heart rate (HR), respiratory exchange ratio (RER) and pulsed oxygen saturation (SpO_2_) will be monitored. Arterial pressure and cardiac output will be noninvasively measured by a finger photoplethysmograpy device (BMEYE, Nexfin HD, Academic Medical Center, Amsterdam, The Netherlands).*Muscle fatigability*Isometric knee extension will be assessed in two ways, first, by measuring the maximum voluntary isometric contraction (MVC), and second, by measuring supramaximal twitch tension (TW) from a series of twitch induced by magnetic stimulation of the femoral nerve (Magstim 200 monopulse Bistim; Magstim Co. Ltd., Whitland, Dyfed, Wales, UK). The occurrence of quadriceps fatigue induced by the exercise regimens will be quantified by measuring the fall in both MVC and TW 15 min after the high-repetitive resistance exercises. Exertional symptoms, that is, perceived dyspnea and muscle fatigue will be quantified with the modified Borg scale.*Exercise stimulus*The exercise stimulus will be quantified from the product of the number of repetitions and the training load. The area under the curve of the tension generated with the elastic bands over time of muscle contractions will also be calculated (BioPac Acknowledge software).

